#### Informal Surveillance of Bullying Behaviors

The level of informal surveillance among employees regarding workplace bullying and harassment will be measured with the four-items adapted from an earlier study in Norwegian Municipalities (Hauan and Klaveness, 2018), assessing the awareness, sensitivity, and responsiveness toward workplace bullying among their colleagues. Example items are “If bullying, harassment, or other negative behavior occurs, employees in my team are quick to notice,” and “Employees who see or notice bullying, harassment, or other negative behavior actively monitor whether the behavior develops.” Responses are given on a five-point Likert scale ranging from 1 “incorrect” to 5 “totally correct.” The scale has in prior research yielded a Cronbach’s Alpha at 0.78 (Hauan and Klaveness, 2018).

#### Bystander Norms

Building on the theoretical model of Ajzen (1991), subjective norms will be measured with two scales. The first scale is *Trust in colleagues* and will be assessed with a four-item scale adapted from Cook and Wall (1980). Example items are “If I am exposed to negative acts at work, I know that my colleagues will try to help me” and “If I am exposed to negative acts, I know I will get support and help to deal with bullying and harassment from my colleagues.” A five-point Likert scale from 1 (“completely disagree”) to 5 (“completely agree”) will be used for responses. The scale reliability was analyzed in the data from the pilot study and showed a Cronbach’s Alpha of 0.78.

The second scale is developed for this project and addresses what the respondents believe will be normative reactions/behavior from colleagues when facing bullying situations. The scale hold nine items, and responses are given on a five-point Likert scale ranging from 1 (“incorrect”) to 5 (“totally correct”). Confirmatory factor analysis was applied to the data from the pilot study. The analysis showed two dimensions, one positive bystander behavior and one negative bystander behavior. The positive bystander behavior contains six items and Cronbach’s Alpha is 0.69, and the negative bystander behavior contains three items and Cronbach’s Alpha is 0.66.

#### Attitude

Building on the theoretical model of Ajzen (1991), attitude will be measured with nine-item scale developed for this project. The scale is similar to that of bystander norms developed for this project, however, whereas the former scale measures respondents’ beliefs regarding colleagues normative reactions/behavior when facing bullying situations, the bystander behavior attitude scale measures a persons’ own usual behavior in bullying situations. An example of one item is “If someone is exposed to negative actions in our team, I may be an active participant in these negative actions myself” (normative behavior from the respondent). Responses are given on a five-point Likert scale ranging from 1 (“incorrect”) to 5 totally (“correct”). Again, confirmatory factor analysis was applied to the data from the pilot study. The analysis showed two dimensions, one constructive attitude bystander and one destructive bystander behavior. The constructive attitude bystander behavior contains six items and Cronbach’s Alpha is 0.89. The destructive attitude bystander behavior contains three items and Cronbach’s Alpha is 0.81.

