### Theoretical Model for the Intervention

The present study builds on the overarching proposition that having bystanders intervene more often and more constructively in everyday bullying and harassment episodes, preferably before the bullying situations have escalated, should help to reduce the occurrence and prevalence of this pertinent problem over time. The present intervention study then builds on the theory of planned behavior (TPB; Ajzen, 1991) to achieve this. The TPB proposes three determinants of a person’s intentions, behavior, and any following behavioral changes, attitude, subjective norms, and perceived behavioral control. These three factors will be seen as proximal and mediating outcomes, while observed and perceived exposure to bullying, including observed social climate, will be the more distal and final focal outcome. In our context, attitude will be addressed by the very nature of the intervention, that is, creating awareness and changes in attitudes regarding the existence and nature of workplace bullying and one’s own attitudes and perceived typical bystander behavior in such situations. The intervention is further designed to alter participants’ subjective norms by increasing the perceived social pressure to perform constructive bystander behavior in such situations. Lastly, by showing when and how bystanders may intervene constructively (Ajzen and Madden, 1986; Ajzen, 1991), the intervention should alter individuals’ perceived behavioral control in specific situations, the latter implying the extent to which the behavior is perceived to be under volitional control. Thus, developing a psychosocial climate in the organization where individual attitudes and social norms foster constructive bystander behavior, while also enhancing the employees’ perceived behavior control as bystanders, is hypothesized to be crucial in combating workplace bullying in organizations.

Accordingly, in addition to investigate any changes in bullying and harassment in the working environment, the present study will examine whether attitudes, social norms, and perceived behavioral control of those who have received an intervention called “Intervene,” will be changed and possibly influence bystander behavior in bullying situations. Ultimately, the intervention should reduce the occurrence of bullying and harassment and improve the social climate at work. As such, we hypothesize the following regarding these proximal outcomes:

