1.Those who have received the intervention will have a change in **outcome variables (behavior)** from T1 to T2 as compared to those in the control group:1.1.Those who receive the intervention will have an increase in *observed workplace bullying* from T1 to T2 as compared to those in the control group due to an increased awareness.1.2.Those who receive the intervention should report lower exposure to bullying behaviors, as compared to those in the control group.1.3.Those who receive the intervention will be more likely to *intervene when observing workplace bullying* from T1 to T2 as compared to those in the control group.2.Those who receive the intervention will have a change in **independent variables (attitudes, norms, perceived control, and social climate)** from T1 to T2 as compared to those in the control group:2.1.Those who receive the intervention will have an increase *in their attitudes toward intervene constructive when observing workplace bullying* from T1 to T2 as compared to those in the control group.2.2.Those who receive the intervention will have an increase in *perceived bystander norms* from T1 to T2 as compared to those in the control group.2.3.Those who receive the intervention will have a more positive view of the *social climate* in the working group from T1 to T2 as compared to those in the control group.2.4.Those who receive the intervention will have an increase in perceived *informal surveillance* from T1 to T2 as compared to those in the control group indicating an increase in social anti-bullying norms in the working environment.2.5.Those who receive the intervention will have an increase in *perceived bystander behavior control* from T1 to T2 as compared to those in the control group.3.From T2 to T3 the control group, which will receive the intervention after T2, will show the same results of the abovementioned hypothesis as the intervention group did from T1 to T2.

An overview of the relationships studied in this intervention is given in Figure 1.

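### The only scale assigned to attitude (hypothesis 2.1) is described as measuring the respondent's own usual behaviour, so a difference on it cannot be read as attitude change

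*Protocol article*

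**What the plan says.** The section Theoretical Model for the Intervention names attitude, subjective norms and perceived behavioural control as the determinants of behaviour and gives them their role: "These three factors will be seen as proximal and mediating outcomes". The hypotheses that follow keep two groups apart. Hypothesis 1 covers behaviour, including (1.3) whether the respondent intervenes. Hypothesis 2 covers "independent variables (attitudes, norms, perceived control, and social climate", and 2.1 predicts a larger rise in attitude towards constructive intervention in the intervention arm between the first and second surveys.

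The Attitude section says that "attitude will be measured with nine-item scale developed for this project". It contrasts this scale with the norms scale, which asks about colleagues, and states that the attitude scale measures the respondent's "own usual behavior in bullying situations". The one item shown includes the words "I may be an active participant in these negative actions myself" and is glossed as "normative behavior from the respondent". The pilot factor analysis is reported as giving "one constructive attitude bystander and one destructive bystander behavior": six constructive items with alpha 0.89 and three destructive items with alpha 0.81.

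Quantitative Data Analysis and Statistics plans indirect effects with the PROCESS script and structural equation models. The Discussion names attitude among the mediators of particular interest.

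**The concern.** In the trial's theory, attitude is how favourably a person evaluates intervening, and behaviour is what the person does. The trial wants to show that the first changes and may influence the second. If the attitude score is in fact a report of usual conduct, two conclusions are at risk:

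- **Hypothesis 2.1.** An arm difference on the scale would be published as a change in attitude when it is a change in what people say they usually do.
- **The attitude-to-intervening path.** It would relate one self-report of the respondent's bystander conduct to another, and part of any association would reflect shared content rather than influence.

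A larger sample does not remove either problem. Hypothesis 3 expects the same pattern in the control group after its delayed intervention, so the same misreading would recur between the second and third surveys.

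**Working it through.** The plan gives no figure on this point, so the check compares sections.

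**1. What the scale is for, and what it is said to measure.** The Attitude section assigns the scale to the attitude determinant and then describes it as own usual behaviour. The example item and its gloss both concern the respondent's conduct. The subscale labels mix the words attitude and behaviour. Nothing in the section describes an evaluation of intervening.

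**2. Whether another instrument fills the gap.** The other instruments described cover exposure to and observation of bullying, self-labelled victimisation, social climate, informal surveillance, trust in colleagues, perceived norms and perceived behavioural control. None is presented as an attitude measure. None of the four content categories listed at the start of Questionnaire Instruments is labelled attitude.

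**3. Whether the article treats attitude and usual behaviour as the same thing.** It does not. Theoretical Model for the Intervention names a person's attitudes and their perceived typical bystander behaviour side by side, and the hypotheses put attitude and behaviour under different headings. The scale is described as measuring typical behaviour.

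**4. What can be computed.** Both subscale scores (6 + 3 = 9 items) and their change between surveys can be calculated and compared between arms. Only their interpretation as attitude fails.

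**5. What happens to the mediation path.** Write *a* for the effect of the intervention on the scale, *b* for the association of the scale with intervening given arm, and *a × b* for the indirect effect in the simple linear case. The outcome in 1.3 is a separate single item under Bullying and Negative Acts, answered yes, no or not observed. Overlap between reported usual conduct and reported intervening can inflate *b*. It does not create *a*: if the intervention leaves the scale unmoved, *a* = 0 and *a × b* = 0 whatever the overlap. If *a* is not zero, an inflated *b* carries through to the indirect effect, which would then be credited to attitude.

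**6. Extent.** One of five hypotheses under heading 2 (2.1 to 2.5), and one of the three determinants.

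**The case against.** Five arguments can be made for the plan.

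- **The scores exist and the outcome is a different variable.** This stands. A reader might infer that the attitude result cannot be derived, or that the model is circular. The documents support neither. The scale is a nine-item, five-point instrument, its example item is conditional in wording, and the intervening item has a different format. The fault is overlap, not identity.
- **Overlap alone cannot produce mediation.** This also stands. A reader might infer that a strong indirect effect would appear by construction, but step 5 shows that an arm effect on the scale is needed as well.
- **Bystander behaviour is a proper mediator in this trial.** The Introduction expects bullying to fall because bystander intervention changes. It would therefore be wrong to infer that the subscales must be dropped from every mediation model. Under a behaviour label they remain legitimate on the path to bullying exposure.
- **The model is openly a modification.** The caption of Figure 1 says so, and typical bystander behaviour is mentioned in the text on attitude. This softens the charge but does not answer it, because the text still names the two as separate things.
- **Only one item is shown.** This is correct. The other eight could contain evaluative content, and the article does not print them. However, the sentence describing the scale covers the whole of it, and it is the article's own statement. It is not a detail lost in condensing.

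The pilot validation does not settle the matter. Factor structure and alpha from 70 health and safety representatives show that the items hang together, not which construct they measure.

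**Conclusion.** The point holds as a contradiction between the described content of the scale and the role assigned to it. As described, hypothesis 2.1 has no measure distinct from behaviour. A difference between arms on the scale is interpretable as a difference in self-reported bystander conduct, and the path from this scale to intervening is confounded by construct overlap. The documents do not allow the size of any inflation to be calculated.

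The severity is moderate. The Abstract and Objectives name bullying and harassment as the main distal outcomes and helping behaviour as the main proximal one, with perceived behavioural control added in the Abstract. None of these depends on this scale, and the comparisons on norms, climate and informal surveillance are also untouched. It would go too far to say that the whole test of the theory fails: one determinant of three loses its stated meaning.

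The conclusion assumes that the article's one-sentence description is accurate for all nine items. If the full questionnaire shows evaluative items among the eight not printed, the conclusion would need to be limited to the remainder.

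**What to change.** **Preferred change.** Rename the two subscales as self-reported constructive and self-reported destructive bystander behaviour. Report them under hypothesis 1, with the constructive score expected to rise and the destructive score to fall. They may stay as proximal mediators towards bullying exposure, as the Introduction intends, but should not be used as an attitude mediator of intervening. Withdraw hypothesis 2.1 and the attitude path, or restate them in terms of behaviour, and say that attitude was not measured separately. This costs only wording and can still be done after data collection.

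**Alternative, only if the first survey has not yet been collected.** Give the same items a stem that asks how right, useful or important it is to act in that way, and keep hypothesis 2.1. The timing matters because Study Design requires an identical questionnaire at every assessment. The cost is that the pilot's two-dimension structure and its alphas of 0.89 and 0.81 would no longer apply and would have to be re-established. Unless the present wording were also kept, the trial would lose the nine-item behaviour score.

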#### Perceived Behavioral Control

Building further on the theoretical model of Ajzen (1991), Perceived behavioral control will be measured with an eight-item scale developed for this project. All items are formulated in behavioral terms and focus on the respondents’ perception of their own ability to handle bullying situations in their team. Example items are “I feel confident in how to handle and intervene in ‘bullying situations’ when they occur” and “I will be able to intervene there and then, if I observe someone being exposed to negative actions by others.” A five-point Likert scale from 1 (“do not agree”) to 5 (“agree completely”) will be used for responses. The scale was tested on the data from the pilot study and Cronbach’s Alpha is 0.86.

### Qualitative Interviews

In the qualitative interview, the selected participants (supervisors, health and safety representatives, and labor union representatives) will be asked to indicate to what extent they think the intervention has had an effect or not, why or why not; and if having an effect, how it has had an effect. More precisely, the qualitative semi-structured focus group interview will be based on the following interview guide:

1. How relevant did you find this intervention in your organization and working environment?2. What do you see as the perceived strengths and limitations of the intervention?3. How effective did you find the intervention when it comes to preventing workplace bullying and harassment in your own department?4. If you found the intervention to be effective, what are the perceived mechanisms that make it effective?5. Are there mechanisms in the intervention, the sessions, or the organization that may act so as to prevent the intervention form being effective?

The last questions will be analyzed to the extent that they talk about mechanisms in the TPB or if they mention other mechanisms. The qualitative focus group interview will be recorded and transcribed. The data will be analyzed using the NVivo 12.1 computer software package.

### Quantitative Data Analysis and Statistics

All variables in the questionnaire will be measured at all times. The dependent variables can be categorical, continuous, time independent, or time dependent. Data will therefore be analyzed using statistical methods adapted to this type of design and variables. Data will be analyzed with SPSS 25.0, Stata 15, MPlus 8.3, and MLwiN 3.04. Following the described aims, this project will determine prevalence rates; group differences; and direct, indirect, and conditional associations between the study variables both cross-sectionally and over time. Group differences will be tested with chi-square tests and ANOVA. Associations between variables will be tested with correlation and regression-based approaches. Indirect and conditional effects will be analyzed with the process script (Hayes, 2013) and structural equation models. Longitudinal associations between variables will be adjusted for stability in variables in order to model changes over time. Latent class analyses will be used to identify latent profiles of exposure and outcome variables among the respondents (Vermunt and Magidson, 2002; Christensen et al., 2018). In order to capture the multilevel structure of the quantitative study data where the measurements (Level 1) of the study constructs are nested within individuals (Level 2), multilevel analyses will be carried out using MLwiN or Mplus depending on the complexity of hypothesized models. Potential control variables and confounders for the adjusted models, e.g., demographic variables, will be considered only when theoretically applicable (Spector and Brannick, 2011).

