## Abstract

**Background:** Workplace bullying is an important and prevalent risk factors for health impairment, reduced workability and lowered efficiency among both targets and observers. Development and tests of effective organizational intervention strategies are therefore highly important. The present study describes the background, design, and protocol of a cluster randomized controlled trial evaluating the effectiveness of an organization-wide intervention on preventing workplace bullying with a focus on promoting active and constructive bystander behavior. The main overarching goal is to develop an easy to use and standardized organizational intervention based on theory and research in the role of bystanders in bullying situations with the potential of reducing the prevalence of workplace bullying. The theoretical framework of the study is theory of planned behavior (TPB; Ajzen, 1991).

**Methods/Design:** Using a full randomized control trial (RCT) design, this project will empirically test the outcomes of an intervention program targeting bullying and harassment as the main distal outcomes and perceived behavioral control and helping behavior among bystanders as the main proximal outcome. A 1-year cluster randomized controlled design will be utilized, in which controls will also receive the intervention. About 1,500 workers from two different locations of a Norwegian industrial company will be randomized into one intervention group and two control groups with at least 400 workers in each group. A survey will be conducted electronically. With a total of three assessments over 10–12 months, the time interval between the measurement times will be 4 months. Thus, the data collection will take place at baseline, completion of the intervention and at 4 months follow-up.

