### Study Design

This project has an RCT design that includes a range of departments from the case company, a Norwegian industry company. The company has two main locations, one on the west coast (location A) being the larger plant with some 1,600 employees and one in mid Norway (location B) being the smaller plant with some 800 employees. In location A, being the larger facility, all departments in the production part and two administrative departments will be randomly assigned to an intervention group and a control group. The control group will receive the intervention 6 months later, as will location B. As such, the location that is given the intervention last (location B) will also serve as an additional control group for the first interventions carried out in location A. Hence, we have two control groups for the initial intervention. In order to carry out a valid and reliable study of causal relationships and mechanisms, it is necessary to use a design where the study variables are measured repeatedly over time. In this project, we will use a mixed method design by combining a longitudinal survey, qualitative interviews, with this RCT design. All employees in the selected departments in the two locations of the case company will be invited to participate in a prospective questionnaire survey that will be distributed three times during a 12-month period. The questionnaire will be identical at all assessment points. It will be possible to distinguish between managers with personnel responsibility, managers without personnel responsibility, safety representatives, labor union representatives, other level employees, and the unit to which they belong. Data will be collected through *Surveyexact*, a web-based system for secure administration of questionnaires. The system is developed for the purpose of tracking individuals over time in a way that satisfies demands for anonymity and personal security and data protection. When accessing the web-based questionnaire by a link, the respondents will be asked to provide their informed consent before responding to the questionnaire. No personally identifiable information about respondents will be available to researchers, as data will be de-identified prior to analyses.

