### Statistical Power

In order to estimate sample size, we conducted a power analysis. One of the primary goals of power analyses is to estimate the number of respondents required in a study to minimize the likelihood of a false negative finding. In the context of intervention studies, the goal is to estimate the number of respondents per group to detect a difference between intervention and control groups. An *a priori* power analysis was conducted using G*Power 3.1.9.2 (Heinrich-Heine-University, Dusseldorf, Germany) with an alpha level of 0.05, power established at 0.80, and an effect size of 0.279. The optimal sample size calculated turned out to be 204 in each sample group (control and intervention group), yielding an optimal total sample size of 408. Based on previous survey studies from Norway in similar settings, the expected response rate is 55–70% at each of the measurement times. For the baseline measurement, the expected response rate will provide a sample size in the area of 750–1,050 respondents. Across all three time points, such a response rate will provide a sample size of about 190–515 respondents. Thus, the intervention study will strive for meeting the high end of the expected response rate of similar studies to meet the estimate from the power analysis and should have no problem in meeting sample sized from T1 to T2. The survey will be conducted electronically. With a total of three assessments over 10–12 months, the time interval between the measurement times will be 4 months.

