
## Strengths and Limitations

The study and its design have several strengths. Through a longitudinal, RCT design, this project performs repeated measurements of social work environmental factors (climates, norms, and trust), bystander behavioral control, intervening variables, and outcomes. This provides more reliable data not only on the possible outcomes of the intervention, yet also on providing possible explanations and moderating psychological factors related to the perceptions, cognitions, emotions, and behaviors of bystanders. As conducting and measuring effects of intervention study on workplace bullying is difficult (Escartin, 2016), prospective designs are the strongest form of scientific evidence for the causal association between organizational interventions and potential effects. Furthermore, the survey builds mainly on well-established and standardized inventories, psychometrically tested for validity and reliability or scales that are tailor-made, yet tested for the present project. The data structure allows for multilevel models where individual level data are aggregated to work units/organizational levels. Depending on the participation, it is likely that the sample will be representative for the case company.

There are also some limitations of the planned project. The included survey instruments are all self-report measures, and the project is thus subject to limitations specific to self-report instruments such as response-set tendencies. The survey data are also measured from the same source, yet at different time points. As such, common method variance may inflate the relations between constructs somewhat (Podsakoff et al., 2003). However, the use of a longitudinal design as well as the opportunity to obtain co-worker reports of working conditions at the team and work unit levels should limit the risk of common method variance caused by self-report biases. Regardless, the main aim of the present study is exactly that, to investigate if a given intervention will change the perceptions of workers regarding their own perceived exposure to bullying, as well as the potential support one may receive from colleagues.

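### Departments are randomised, but no specified test of the intervention effect includes a department level, so type I error exceeds 5% whenever outcomes (or changes in them) vary between departments

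*Protocol article*

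**What the plan says.** The Abstract describes the design as clustered: "A 1-year cluster randomized controlled design will be utilized". Study Design names the unit for location A: "all departments in the production part and two administrative departments will be randomly assigned to an intervention group and a control group". Delivery is clustered too. The Intervention section describes sessions for work-teams of 15–30 employees, followed by guidelines written for the department.

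Quantitative Data Analysis and Statistics then sets out the methods:

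- "Group differences will be tested with chi-square tests and ANOVA".
- Associations are tested by correlation and regression, and longitudinal associations are adjusted for stability.
- "Indirect and conditional effects will be analyzed with the process script (Hayes, 2013) and structural equation models".
- Latent class analysis is used for profiles.
- The multilevel structure has two numbered levels: "where the measurements (Level 1) of the study constructs are nested within individuals (Level 2), multilevel analyses will be carried out".

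The only mention of a level above the person is in Strengths and Limitations: "The data structure allows for multilevel models where individual level data are aggregated to work units/organizational levels". Study Design says that each respondent's unit will be identifiable.

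**The concern.** In a cluster randomised trial, the arm contrast is estimated between departments. Its standard error must therefore carry the variation between departments. Chi-square tests and ANOVA on workers treat respondents as independent. A random effect for the person handles repeated answers from one worker, but it leaves workers in the same department independent of each other. In either analysis, variation between departments is spread over several hundred workers as if it were individual noise, and intervals come out too narrow.

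Much is at stake. Hypotheses 1.1 to 2.5 are all contrasts of intervention with control. The Dissemination section says the company will use the findings to decide on wider implementation. The Introduction presents the trial as an answer to the field's shortage of rigorous designs.

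This is not detail that a condensed article may leave to a fuller plan. The article names the tests and numbers the levels, and what it fixes does not match the unit it randomises.

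**Working it through.** **1. The plan's own figure.** Statistical Power states a calculation "with an alpha level of 0.05, power established at 0.80, and an effect size of 0.279", giving 204 per group. For two independent means, n = 2(1.96 + 0.842)² / 0.279² = 15.70 / 0.0778 = 201.7, so 202 per group. The exact t calculation gives 203. One-sided, the figures would be 159 and 160. The stated 204 is therefore, to within rounding, a two-sided calculation on independent individuals with a design effect of 1. It makes the same assumption as the analysis section.

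**2. Effect of leaving the department out.** With m respondents per department and intraclass correlation ρ, the variance of an arm mean is multiplied by DE = 1 + (m − 1)ρ. A test that ignores this has true two-sided error 2[1 − Φ(1.96/√DE)].

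Inputs: 204 per arm is from the article. The number of departments per arm and ρ are assumptions, because the article gives neither. With 5 departments per arm, m = 204/5 = 40.8. With 12 per arm, m = 204/12 = 17.

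| Departments per arm | ρ | DE | 1.96/√DE | True error |
|---|---|---|---|---|
| 5 | 0.01 | 1 + 39.8 × 0.01 = 1.398 | 1.658 | 9.7% |
| 5 | 0.02 | 1.796 | 1.463 | 14.4% |
| 5 | 0.05 | 2.990 | 1.133 | 25.7% |
| 12 | 0.01 | 1 + 16 × 0.01 = 1.160 | 1.820 | 6.9% |
| 12 | 0.02 | 1.320 | 1.706 | 8.8% |
| 12 | 0.05 | 1.800 | 1.461 | 14.4% |

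Simulation of an individual-level test at 204 per arm gave the same rounded values: 10%, 14% and 26% with 5 departments, and 7%, 9% and 14% with 12. A second simulation at 400 per arm, with 10 departments of 40, gave 5.3%, 9.6%, 15.0% and 25.3% at ρ = 0, 0.01, 0.02 and 0.05. With ρ = 0 the nominal level is kept.

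**3. Change contrasts.** The table describes one time point without adjustment. For T2 minus T1 with complete pairs, a stable department effect cancels. The formula still applies, but ρ becomes the ICC of the change, which comes only from departments moving differently over time. That may be smaller than the cross-sectional ICC, and the article gives no value. If it is zero, the error is 5%.

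**4. Power once clustering is allowed for.** At 204 per group the standardised effect is 0.279 × √(204/2) = 2.818. Power is Φ(2.818/√DE − 1.96). With 5 departments per arm this is about 66%, 56% and 37% at ρ = 0.01, 0.02 and 0.05. With 12 per arm it is about 74%, 69% and 56%. The nominal figure is 80%. These are large-sample values for an unadjusted single-time-point test, and adjusting for T1 would recover some power.

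**5. Small numbers of departments.** In the simulation at 204 per arm, a t-test on department means held 5%, while a normal reference distribution on the same means gave 6–9%. A department term alone is not enough, and the reference distribution also has to reflect how few departments there are.

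**The case against.** The strongest reply is that the article lists a broad toolkit. It names regression, structural equation models and latent class analysis, and says MLwiN or Mplus will be used according to model complexity. Unit membership is recorded, and Strengths and Limitations acknowledges that work-unit models are possible. The sentence on chi-square tests and ANOVA refers to group differences in general and is not expressly tied to the arm contrast. All of this is fair, and it shows that the remedy is within reach. It does not supply the remedy. No listed method is linked to departments, the one model whose levels are spelled out ends at the individual, and a remark about what the data permit is not a planned test.

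Three stronger readings are tempting and not supported.

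- *That the plan ignores baseline.* The same section adjusts longitudinal associations for stability, and the repeated-measures model includes T1. At most, the article does not say which method tests the effect.
- *That the error rates in the table apply to the trial's hypotheses as they stand.* Hypotheses 1 and 2 are framed as T1-to-T2 changes, where only department-by-time variation inflates the error. Group delivery does not by itself create such variation when the intervention has no effect in any department. It would have to come from other local changes, or from effects that differ between departments. Both are plausible, and neither is quantified.
- *That inflation is certain.* It needs a positive ICC. Shared ratings such as social climate, informal surveillance and colleagues' norms make one likely, but the article reports none.

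**Conclusion.** The concern stands and should be settled before analysis. The Abstract and Study Design make the department the randomised unit, and the analysis section specifies no test of the arm contrast that contains it. The direction is clear: standard errors are too small, and the type I error is above 5%, whenever outcomes vary between departments or, for change analyses, whenever departments change differently over time.

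The size is not known. The illustrative range of about 7% to 26% rests on 204 per arm, 5 or 12 equal departments per arm, ICCs of 0.01 to 0.05, and an unadjusted test at one time point. Change contrasts may suffer less.

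**What to change.** In Quantitative Data Analysis and Statistics, state that every randomised intervention-versus-control contrast at location A is tested in a model that includes the randomised department. Choose one of two forms in advance. They are different estimators, so the choice should be stated:

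- the T2 value on arm, adjusted for the T1 value, with a random effect for department; or
- a three-level model (measurement, person, department) with a department-by-time random effect.

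Specify small-sample inference, for example Kenward-Roger for linear models and a department-level permutation test for categorical outcomes. For indirect effects, use multilevel structural equation models or another method that accounts for departments. Keep chi-square tests and ANOVA for description. Report the number of departments per arm and the estimated ICCs.

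Report the comparison with location B separately and label it non-randomised. It is a single site that was not allocated at random, and a department term does not repair that.

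No change to recruitment, delivery or the questionnaire is needed. Unit membership is already recorded, and the plan already lists multilevel software. The cost is wider confidence intervals and less power than the unclustered 204 per group implies, which Statistical Power should acknowledge.
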